The European Union Horizon 2020-funded TRANS-FOODS project aims to understand the exact mechanisms behind transcutaneous sensitization and to develop and test novel prevention approaches. Here we present the protocol for an intervention study that forms part of the TRANS-FOODS programme of work to examine the immune responses to peanut allergens in individuals with and without AD, with and without skin massage. Specifically, we aim to determine whether peanut allergen components can penetrate the skin through regular massage and whether this effect is amplified in individuals with a compromised skin barrier. We will also investigate whether preapplication of a barrier-enhancing cream can reduce transcutaneous uptake of peanut proteins.

The primary objective of this study is to determine whether inflammatory cytokines, such as interleukin (IL)-4 and IL-13 can be detected in skin interstitial fluid (ISF) after regular massage using a peanut protein-containing extract.

The secondary objectives are:

To clarify whether this effect is amplified in those with an ­impaired skin barrier (patients with AD vs. healthy control ­p­articipants).To test whether peanut protein components present in skin ISF are able to induce activation of basophils in blood of ­donors allergic to peanuts.To assess whether the transcutaneous uptake of peanut protein can be reduced by the prior use of a barrier-enhancing cream.

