### Endpoints

The primary endpoint will be the change from baseline in inflammatory cytokine concentrations (interferon-γ, IL-10, IL-12p70, IL-17, IL-1β, IL-2, IL-4, IL-6 and tumour necrosis factor-α) in skin ISF following regular massage with a peanut protein-containing extract.

The secondary endpoints will be the potential detection of peanut protein components in retrieved skin ISF. If detected, we will also measure whether the retrieved peanut protein can activate mast cells and basophils, comparing the study arms. Raised TEWL will also be a secondary endpoint.

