### Sample size

Our previous studies indicate that the coefficient of variation of ISF cytokines from ISF is ∼20%, peanut protein in skin samples is ∼8% and BAT/MAT from ISF ∼30% (unpublished data). In all these cases a group size of 15 will provide over 90% power to detect a doubling of concentration levels. Allowing for approximately 8% dropout, 65 participants will be needed in the healthy skin and AD groups (130 total).

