### Statistical methods

Comparison of baseline demographic characteristics of study participants across all eight intervention groups will be done using descriptive methods. Adherence to the intervention, including the reasoning behind noncompliance, withdrawal from the study and loss to follow-up, will be summarized. Any adverse events reported by study participants through the daily record surveys or within the visits will also be summarized.

Descriptive and inferential methods will be used for the main analysis. The primary analysis will comprise analysis of covariance to estimate the difference in concentration of inflammatory cytokines in skin ISF between massaging and no massaging patients as per the primary objective by intention-to-treat at week 4. The terms in the model will include the effects of having impaired skin, use of barrier-enhancing cream and massage. Covariates such as gender, ethnicity, baseline TEWL and baseline values of the outcome will be included, with TEWL considered a key mediating factor. Secondary outcomes, including the effect of impaired skin, use of barrier-enhancing cream, and basophil and mast cell activation, and peanut-specific IgE levels, will be analysed similarly. Interaction effects, including those involving massage frequency (categorical and continuous), will also be tested, with significance levels set at 5% for main effects and 10% for interactions. Analyses will account for non-normal data using transformations or nonparametric tests like the Wilcoxon–Mann–Whitney test.

The proportion of participants lost to follow-up after randomization will be summarized in each intervention group. This ­summary will include reasons for loss to follow-up including ­participant withdrawal, withdrawal by the clinical study team and other specified reasons. Baseline characteristics of those missing a week 4 assessment for healthy vs. skin impaired volunteers, cream application vs. no barrier-enhancing cream and massaging vs. no massaging will be compared descriptively to those with complete follow-up at week 4. There will be no imputation for missing data.

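### Nine unranked cytokines form the primary endpoint under a flat 5% level: if each massage effect is tested at that level, the chance of at least one false-positive primary result is up to 37%

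*Protocol article*

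**What the plan says.** Endpoints in the protocol article: "The primary endpoint will be the change from baseline in inflammatory cytokine concentrations", followed by the list "interferon-γ, IL-10, IL-12p70, IL-17, IL-1β, IL-2, IL-4, IL-6 and tumour necrosis factor-α". That is nine analytes. No lead cytokine, order of testing, composite or required number of positive results is given.

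Statistical methods: the primary analysis is an analysis of covariance at week 4 to "estimate the difference in concentration of inflammatory cytokines in skin ISF between massaging and no massaging patients". On the model it adds: "The terms in the model will include the effects of having impaired skin, use of barrier-enhancing cream and massage". Only massage is the primary contrast. The error rule is "significance levels set at 5% for main effects and 10% for interactions". Sidedness is not stated.

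Secondary objectives, at the end of the introduction: the first is "To clarify whether this effect is amplified in those with an" impaired barrier, that is, patients with AD against healthy controls. The primary objective just above it gives IL-4 and IL-13 as examples. IL-13 is not in the Endpoints list.

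Sample size: "Our previous studies indicate that the coefficient of variation of ISF cytokines from ISF is ∼20"%, and "a group size of 15 will provide over 90% power to detect a doubling of concentration levels". This is power for a single comparison.

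**The concern.** The protocol fixes a per-test level but does not say what carries the primary conclusion. Nine analytes have equal standing, and the only threshold given is 5% for a main effect. Followed as written, the rule lets a single cytokine crossing 5% be presented as a primary finding, and with nine chances the error for the family is well above 5%. The Discussion part of the Abstract presents the study as the first of its kind, so a positive massage effect would have little earlier evidence to be judged against.

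A second, separate question concerns the 10% level. Whether the massage effect is larger in AD than in healthy skin is a difference of differences, so in this model it is a massage-by-AD interaction. A named secondary objective would then be judged at 10% in each of nine cytokines.

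**Working it through.** **Inputs.** From the article: nine cytokines (Endpoints); 5% and 10% (Statistical methods); CV about 20%, 15 per group and a doubling (Sample size); eight groups of 15, hence 120 analysed, 60 massage against 60 no massage, and 30 in each massage-by-AD cell (Intervention). Assumed here: two-sided tests, a log-scale analysis, and the correlations between cytokines, which the article does not give.

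**1. The plan's own figure.** The SD on the log scale is √ln(1 + 0.20²) = 0.198. With 15 per group the standard error is 0.198 × √(2/15) = 0.0723, and ln 2 / 0.0723 = 9.6. Power at 5% exceeds 99.9%, so the claim of over 90% is reproduced.

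**2. Family-wise error for the primary contrast.** Nine independent tests at 5%: 1 − 0.95^9 = 1 − 0.630 = 0.370. By the Šidák inequality this is the ceiling for two-sided tests on jointly normal statistics. With no assumption on dependence the bound is 9 × 0.05 = 45%. Simulation of nine equicorrelated normal statistics (400,000 runs) gives:

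| Assumed correlation | At least one false positive |
|---|---|
| 0 | 37.0% |
| 0.3 | 32.6% |
| 0.5 | 26.8% |
| 0.7 | 20.2% |
| 0.9 | 12.3% |

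**3. The interaction, kept apart from step 2.** One massage-by-AD test per cytokine at 10%: 1 − 0.90^9 = 1 − 0.387 = 0.613 if independent, and less under positive correlation.

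**4. Effect of a correction.** Bonferroni uses 0.05/9 = 0.0056 per cytokine. The family-wise error becomes 1 − (1 − 0.0056)^9 = 4.9% under independence and is at most 5% in general.

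**5. Cost for the massage comparison.** For the planned doubling with 15 per group at CV 20%, power stays above 99.9% at 0.0056. For 60 against 60 the standard error is 0.198 × √(2/60) = 0.0362. Using the t distribution with 118 df, the log difference detectable with 90% power is 0.118 at 5% (ratio 1.125, about 1.13) and 0.149 at 0.0056 (ratio 1.16).

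**6. Cost for the interaction.** The standard error is 0.198 × √(4/30) = 0.0723. By the normal approximation, for two illustrative ratios that are not in the article:

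| Interaction ratio | ln(ratio)/SE | Power at 10% | Power at 5% | Power at 0.0056 |
|---|---|---|---|---|
| 1.2 | 2.52 | 81% | 71% | 40% |
| 1.3 | 3.63 | 98% | 95% | 80% |

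The last column is plain Bonferroni over nine. Holm loses no more than this.

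**The case against.** The strongest reply is that much of this is inferred from silence. The article does not say in words that each cytokine is tested separately, nor that one significant cytokine makes the trial positive. The stated aim of the covariance analysis is to estimate a difference. A correction procedure commonly sits in a statistical analysis plan, which is not shown, and a nominal 5% level is compatible with a later adjustment. All of this stands as a limit on the claim: the 37% is conditional on testing each cytokine at 5%. It does not remove the point, because the protocol is not silent on the error rule. It fixes flat levels over an unranked primary endpoint. An analysis plan that followed the rule would inherit the problem, and one that controlled the family would have to go beyond it.

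Four stronger readings are tempting, and the article does not support them.

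- A reader might infer that the 10% level feeds the 37%. It does not. The 37% comes only from nine 5% tests of massage, and interactions are not the primary contrast.
- A reader might take the 10% test of the first secondary objective as stated. The article never assigns that objective to the interaction tests, and it lists the effect of impaired skin among secondary outcomes analysed in a similar way. The interaction is the natural reading, not an explicit one.
- A reader might infer that the relaxed level buys nothing. That depends on the ratio chosen: at 1.3-fold the 10% level adds about 3 points over 5%, but at 1.2-fold it adds about 10.
- A reader might think that an IL-4 and IL-13 primary family needs only a change of wording. IL-13 is not among the nine listed cytokines, so using it changes the endpoint and possibly the assay panel, whose analytes the article does not list.

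**Conclusion.** The concern holds in conditional form. With nine unranked cytokines in the primary endpoint and a flat 5% level for main effects, testing the massage effect in each gives a family-wise error of up to 37%. The figure assumes independent two-sided tests. The true value depends on correlations that the article does not give, and even at 0.9 the error is 12%, more than twice the nominal level. It is not shown that the trial will declare success on one cytokine, only that nothing in the stated rule prevents it.

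Separately, if the first secondary objective is tested as a massage-by-AD interaction under the stated rule, the chance of at least one false finding of amplification is up to 61% across nine cytokines. This is a secondary-objective error and should not be merged with the primary figure.

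**What to change.** 1. Control the primary massage comparison at an overall two-sided 5% over the nine listed cytokines, by Holm or by Bonferroni at 0.0056 each. Alternatively, name one listed lead cytokine, such as IL-4, and make the others secondary.
2. Reconcile the primary objective, which names IL-13, with the Endpoints list, which omits it, before IL-13 enters any primary family.
3. State that the first secondary objective is carried by the massage-by-AD interaction, and test it at an overall 5% with the same multiplicity control. Testing it at 5% in each of several cytokines would not be enough: two independent tests already give 1 − 0.95² = 9.75%.
4. Label all other interactions, including those with massage frequency, exploratory and report them with confidence intervals.

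For the nine listed cytokines this is a wording change and needs no extra participants on the plan's own inputs. The massage comparison loses little: the ratio detectable with 90% power moves from about 1.13 to 1.16, and power for a doubling stays above 99.9%. Small interactions lose more. For a 1.2-fold ratio, power falls from about 81% to 71% at a single-test 5% level and to about 40% under Bonferroni over nine. A single lead cytokine avoids that last step.

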### Monitoring

A Study Steering Committee (SSC) has been established for the TRANS-FOODS project and is chaired by the Chief Investigator, providing full oversight of the project, including this trial. The SCC includes members of the clinical study team, all principal ­investigators and their respective teams within the TRANS-FOODS consortium, as well as patient and public involvement representatives. Meetings are every 4 months throughout the project and allow all partners to provide feedback on study findings and plans.

An Independent Data Monitoring Committee (IDMC) has also been set up for the study and is comprised of an independent chairperson, plus two independent members: one who is an expert in the field of paediatric dermatology and one who is an expert in medical statistics. Meetings are held biannually throughout the project, with the Chief Investigator, members of the clinical study team and the trial statistician in attendance. Prior to the IDMC meeting, the study statistician will formulate open and closed reports. The IDMC is responsible for reviewing these and assessing recruitment, interim monitoring of safety and effectiveness, trial conduct and external data. The IDMC will provide a recommendation to the SCC concerning the continuation of the study.

### Adverse events reporting and harms

The study is low risk, and no major adverse events are expected. Nonetheless, the safety of the peanut protein-containing solution and barrier-enhancing cream will be monitored throughout the study. We will ask participants to report any adverse events to us through the daily record survey which they will be sent electronically through the REDCap database system. Participants will also be informed to report adverse events by contacting us directly via the study email or let us know during the study visits. Any adverse events will be recorded on the REDCap database system using the standardized MedDRA protocol.

### Trial registration

The trials are registered on ISRCTN (ISRCTN12492694) and ClinicalTrials.gov (NCT05407012).

### Ethics and dissemination

#### Public and patient involvement

This project was developed through a collaborative effort involving members of the consortium, as well as contributions from allergy sufferers, their families, patient organizations, and charities such as the National Eczema Society and Allergy UK. Patient representatives from the National Eczema Society and Allergy UK are also invited and involved in the SCC meetings as outlined above.

#### Protocol amendments

The original version of this protocol was prepared in January 2023 and there has been one amendment since then. The amendment provided updates on study procedures. As of 28 August 2024, ­v­ersion 2.0 is effective.

If further amendments to this protocol are required, approval will be sought from the King’s College London Research Ethics Committee. The revised version of the protocol will be filed in the Investigator Site File, and corresponding updates will be made to the consent forms and clinical trial registry entry.

#### Consent

Written informed consent will be obtained from all those participating in the study. Prior to this, the participant information sheet and a discussion of objectives, risks and inconveniences of the study will be provided to participants by delegated, trained staff members with experience in obtaining informed consent.

#### Confidentiality

All clinical study staff will ensure to protect the participants’ privacy and consent rights in accordance with the Data Protection Act 2018. Access to study information will be limited to clinical study staff and investigators.

#### Ancillary and post-trial care

It is not anticipated that participants will require post-trial care as they will stop using the intervention after their final visit. However, participants will be advised to contact the study research team via the designated study email address if they experience any symptoms related to the application of the intervention after completing the trial. In such cases, a dermatologist within our team will assess the participant.

#### Data dissemination

The results of the study will be reported and disseminated in peer-reviewed scientific journals and/or conference presentations. Participants will be sent a lay summary of the study results.

## Data Availability

No new data have been generated.
